### Data collection methods

The baseline and final visits will be at the participant’s designated GP practice. Anthropometric measures (height, weight and waist circumference), blood pressure and pulse will be collected by the diabetes nurse or the practice nurse at the GP practice. Questionnaires (medical history, medicine use, dietary intake and participant characteristics) will be sent to the participants’ nominated address. Participants can nominate to complete the majority of surveys online if they choose to do so. The adverse event questionnaire, blood request forms and new supply of supplement capsules will be mailed to participants every 3 months with a reply-paid envelope. Participants will return the questionnaire along with any remaining capsules previously supplied for research staff to record any adverse events and to record compliance using pill counts; participants will also undergo blood tests at their nearest pathology provider. The timeline for collection of the various data points is shown in Fig. 2.

**Fig. 2 Fig2:**
[figure not shown]
Trial design. Simplified schematic of trial design

### Data management

An online REDCap database will store all data collected. This database will be managed by an independent statistician.

### Statistical methods

Analyses will be undertaken in accordance with the Consolidated Standards of Reporting Trials (CONSORT) guidelines by an independent statistician blinded to treatment group allocation [22].

#### Effectiveness of zinc

##### Primary analysis

IS and HbA1c at baseline and at 1, 6 and 12 months will be plotted to assess response trajectories. We will fit a linear mixed model (LMM) with IS or HbA1c measured at 1, 6 and 12 months as the dependent variable and fixed effects for time (categorical predictor), group and time-by-group interaction terms. This will allow us to identify the time points at which maximal group differences are observed, although the primary outcomes will be judged at 6 months. A random intercept will be included to account for repeated measures on participants, and the model will be adjusted for baseline HbA1c or IS, age, sex, physical activity and diet. The LMM uses all available values for each participant and provides robust effect estimates assuming data are missing at random. All statistical analyses will observe the intention-to-treat principle. A significant difference on either of the primary outcomes will be sufficient to declare an effect, although we will also look at consistency in the direction of the secondary outcomes.

##### Secondary analyses

A similar LMM approach will be used to jointly analyse the data at baseline and 1, 6 and 12 months for insulin resistance, beta-cell function, lipids and other secondary outcomes across the zinc and control groups.

#### Effectiveness of Get Healthy T2DM Prevention Program

HbA1c values at baseline and at 1, 6 and 12 months will be plotted for the placebo group alone to allow us to describe the effect of the Get Healthy Information and Coaching Service without zinc supplementation. We will fit an LMM with fixed effects for time as a categorical predictor and HbA1c as the dependent variable. This will allow us to estimate the mean within-person pre-post differences due to lifestyle changes. A random intercept will be included to account for repeated measures on participants, and the model will be adjusted for baseline age, sex, physical activity and diet quality.

A similar LMM approach will be used to analyse IS and FBG and to jointly analyse the baseline and 12-month data for BMI, waist/hip ratio and blood pressure. In addition, completion rates for the Get Healthy Information and Coaching Service for those referred as part of the study will be benchmarked to current rates for those referred through other sources.

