## Background

The global burden of diabetes (among adults aged 20–79 years) in 2015 was estimated at US 415 million and is expected to rise up to 642 million by 2040 [1–3]. The global health cost in 2015 was approximately US $673 billion with an expected 25.4% increased cost to US $802 billion in 2040 [2]. The number of deaths attributed to diabetes worldwide in 2015 was 5 million [2]. It is known that 90–95% of diabetes cases are type 2 diabetes mellitus (T2DM), which is a preventable and modifiable disease [1]. Pre-diabetes mellitus (PreDM) is a potentially reversible condition of impaired glucose handling. It is increasingly being diagnosed on the basis of a haemoglobin A1c (HbA1c) measurement, given the low coefficient of variation of this test [4]. The natural history of PreDM is variable; progression to T2DM occurs in ~ 25%; the abnormal glycaemic state remains in 50%; and reversion to normal glycaemic state occurs in 25% over 3–5 years [5]. People with PreDM are 5–15 times more likely to develop T2DM and are at increased risk of cardiovascular disease (CVD) [6]. The progression of disease through the pre-diabetic phase provides an opportunity to intervene to reduce or delay the onset of frank diabetes.

Interventions for PreDM are limited. Improving lifestyle factors, such as nutrition and physical activity, and maintenance of healthy weight have been found to reduce the progression from PreDM to T2DM by ~ 50%, although these changes take time to institute and are often difficult to maintain for the long term [7]. Despite the effectiveness of interventions to reduce such risk factors, the prevalence/incidence of obesity and PreDM continues to increase globally and in Australia [2, 8]. Given this trend, additional and complementary treatment options that will prevent, or at least delay, progression of PreDM are needed. Our intervention will involve the referral of all participants to an existing health promotion programme provided by the NSW State Health Department: the Get Healthy Information and Coaching Service [13]. The free telephone coaching service contacts participants on up to 13 occasions over the first 6 months of the study to encourage lifestyle improvements. In addition, participants will be randomised to receive either a zinc or placebo daily supplement.

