### Trial design

The study will be a double-blind, randomised, parallel-group, placebo-controlled superiority trial. The allocation ratio will be 1:1 zinc supplementation and placebo, stratified by GP practice and biological sex (male and female). Participants will be followed up at 1 month, 6 months and 12 months. Both treatment arms will be referred to the Get Healthy Information and Coaching Service type 2 diabetes prevention program for the first 6 months of the trial (standard duration of the programme). The schematic of the trial recruitment is provided in Fig 1.

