### Eligibility criteria

#### Inclusion criteria

To be eligible, men and women aged 40–70 years and with a body mass index (BMI) ≥ 28 kg/m^2^ will be screened for PreDM on the basis of one HbA1c measurement (5.7–6.4 mmol/L) as per the American Diabetes Association guidelines [19]. Potential participants must be willing to enrol in the Get Healthy Information and Coaching Service and not meet any of the exclusion criteria.

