### Interventions

All participants will be enrolled in the Get Healthy Information and Coaching Service. This is a registered service run by the New South Wales state health department that provides up to 13 telephone calls over 6 months from allied health professionals who provide health information and support participants to achieve a better lifestyle; it focuses on diet, physical activity, smoking cessation and alcohol reduction [13].

The intervention group will receive a daily oral zinc gluconate capsule (30 mg of elemental zinc, provided by Blackmores, Sydney, Australia) to be consumed before breakfast for a period of 12 months. The placebo group will receive a cellulose capsule (appearance identical to the zinc capsule) to be taken similarly.

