#### Modelled analyses

The results of the trial-based analysis will be extrapolated in a cost-consequence analysis comparing the health care resource use profiles for two cohorts over a 5-year period: those people with delayed progression to diabetes as a result of zinc supplementation in conjunction with effective lifestyle modification and those people who follow the natural history of diabetes progression.

A second modelled analysis will extrapolate the results from the trial-based analysis and transform the intermediate, primary trial outcome into a final, patient-relevant outcome: quality-adjusted life-years saved. The cost-utility analysis will model costs, expected cost savings and patient outcomes over the lifetime of a hypothetical cohort of patients with PreDM. Similar direct and modelled analyses will be performed for the evaluation of the Get Healthy Information and Coaching T2DM Prevention Program, looking at pre- and post-glycaemic markers.

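### The before-after change in the placebo arm is read as the effect of coaching and carried into economic models, but the trial has no contrast that isolates coaching

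*Protocol article*

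**What the plan says.** The section on the effectiveness of the Get Healthy programme states that HbA1c "will be plotted for the placebo group alone to allow us to describe the effect of the Get Healthy Information and Coaching Service without zinc". A linear mixed model with time as a categorical effect follows, adjusted for age, sex, physical activity and diet quality, and of this model the article says: "This will allow us to estimate the mean within-person pre-post differences due to lifestyle changes".

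No participant goes without coaching. Under Interventions: "All participants will be enrolled in the Get Healthy Information and Coaching Service". Under Trial design: "Both treatment arms will be referred to the Get Healthy Information and Coaching Service type 2 diabetes prevention program for the first 6 months of" […]. A matching secondary objective compares the control group with its own baseline.

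Entry depends on the variable that is later analysed: people are "screened for PreDM on the basis of one HbA1c measurement", in the range 5.7 to 6.4 (Inclusion criteria). The legend to Fig. 1 lists HbA1c both at a pre-allocation point and at t0, which it labels baseline. It also places the baseline assessments at the pre-allocation point.

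Under Modelled analyses: "Similar direct and modelled analyses will be performed for the evaluation of the Get Healthy Information and Coaching T2DM Prevention Program", using glycaemic markers before and after.

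**The concern.** The quoted sentence is a causal claim about an uncontrolled comparison. A change from baseline in people who all receive coaching and placebo capsules is the sum of any coaching effect, the natural course of pre-diabetes, placebo response and the effect of being in a trial. If the baseline is the value that qualified the person for entry, regression to the mean is added. Adjusting for age, sex, physical activity and diet quality separates none of these from coaching. The only external benchmark in that section concerns completion rates of the service, not glycaemia.

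The secondary objectives include whether coaching alone improves glucose handling, and the cost-effectiveness of the new model of care. Followed as written, the plan could report a coaching benefit that the design cannot identify, and then extrapolate it in models that reach to lifetime quality-adjusted life-years.

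**Working it through.** **The plan's own figure.** The Sample size section gives a difference of 0.3 and SD 0.7 in insulin sensitivity, alpha 0.01 and power 0.9.
- Two-sided normal formula: n = 2 × (2.576 + 1.282)² × 0.7² / 0.3² = 162.0, rounded up to 163 per group.
- With the t distribution: 163.7, rounded up to 164 per group, as stated.
- With 20% loss: 164 / 0.80 = 205 per arm, 410 in total, as stated.

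These numbers concern the randomised zinc comparison. The article gives no figure for the before-after analysis, so 164 is used below as the number of placebo participants analysed.

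**Is there a contrast for coaching?** Coaching is present in both arms. The zinc-minus-placebo difference therefore says nothing about coaching, and the placebo arm taken alone has no concurrent comparator. This part of the point needs no arithmetic.

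**Natural history.** The Background says that "reversion to normal glycaemic state occurs in 25" per cent over 3 to 5 years, and in the same sentence that about 25% progress to diabetes. Spontaneous change thus goes both ways, over a longer period than this 12-month trial. It is a reason not to attribute the change to coaching, but it does not show the direction of the bias.

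**Regression to the mean, if the qualifying value is the baseline.** The article gives no HbA1c mean or SD, so these are assumptions: mean μ of the screened population 5.5 to 5.8, between-person SD σ_b 0.30 to 0.40, within-person SD σ_w 0.10 to 0.20. The coaching effect is set to zero. Selection is on an observed value X between 5.65 and 6.45 (the entry window, allowing for rounding).
- s² = σ_b² + σ_w² and ρ = σ_b² / s².
- Expected change at retest = −(1 − ρ) × (E[X | selected] − μ), with the mean of a truncated normal distribution.
- SD of change = √[(1 − ρ)² Var(X | selected) + s²(1 − ρ²)].
- z = change / (SD / √164).

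| μ | σ_b | σ_w | ρ | E[X given selected] | Change | SD of change | z | Chance of p < 0.05 |
|---|---|---|---|---|---|---|---|---|
| 5.5 | 0.30 | 0.20 | 0.69 | 5.88 | −0.117 | 0.27 | −5.6 | about 100% |
| 5.6 | 0.30 | 0.15 | 0.80 | 5.89 | −0.058 | 0.20 | −3.7 | 96% |
| 5.8 | 0.30 | 0.15 | 0.80 | 5.96 | −0.031 | 0.21 | −1.9 | 49% |
| 5.8 | 0.40 | 0.10 | 0.94 | 5.98 | −0.011 | 0.14 | −1.0 | 17% |
| 6.05 | any | any | – | 6.05 | 0 | – | 0 | 5% |

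First row in full: s² = 0.09 + 0.04 = 0.13; 1 − ρ = 0.04 / 0.13 = 0.308; 0.308 × (5.881 − 5.5) = 0.117; standard error 0.2658 / √164 = 0.0208; z = −5.6. The first and fourth rows are the extremes of the assumed range.

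**If baseline is a separate sample.** With μ 5.6, σ_b 0.30, σ_w 0.15, a simulation of 4,000,000 people gave −0.058 when the qualifying value was the baseline and 0.000 when a fresh value was. The artefact depends entirely on which value is analysed.

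**The case against.** Several counter-arguments have force.

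- *Baseline.* Nothing in the article says that the qualifying value is the analysed baseline, and the Fig. 1 legend lists a t0 sample. A reader might infer that regression to the mean will certainly be counted as a coaching effect. The text does not support that; it leaves the matter open, and with a fresh baseline the artefact is zero.
- *Size.* The screened group has BMI of at least 28 and age 40 to 70, so its HbA1c mean may well lie above 5.7, and the Background describes the variability of the test as low. Both push the artefact towards the lower end of the range. This stands, and is why the range extends down to 0.01.
- *Natural reversion.* A reader might count the 25% reversion as spurious benefit. It refers to 3 to 5 years and is matched by about 25% progression, so natural history could also hide a benefit.
- *Zinc model.* The cost-consequence model describes "those people with delayed progression to diabetes as a result of zinc supplementation in conjunction with effective lifestyle modification" and sets them against natural history. A reader might infer that the model selects successes and credits coaching to zinc. The documents do not support this: the Direct analyses section uses the zinc group against the placebo group, the model is said to extrapolate that result, and the wording names the combination rather than zinc alone. Only a clarification is warranted.
- *Scope.* The comparison is a secondary objective and is openly described as one with own baseline. True, but the article still calls the result due to lifestyle changes and builds economic analyses of the programme on before and after markers.

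**Conclusion.** The point holds as one of attribution. The protocol article draws a causal conclusion about coaching from an uncontrolled before-after change and uses before and after markers in the economic evaluation of the programme. That conclusion is unsupported whichever HbA1c value is the baseline, because natural course, placebo response and trial participation remain mixed in.

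Regression to the mean is a conditional addition. If the qualifying HbA1c is the baseline, the spurious fall is about 0.01 to 0.12 points, |z| about 1.0 to 5.6 with 164 participants, under the assumed means and SDs. The chance of a nominally significant fall with no coaching effect then runs from about 17% to nearly 100%. If the screened population is centred at 6.05, or baseline is a separate sample, it adds nothing. The randomised zinc comparison and the trial-based zinc cost-effectiveness ratio are not affected.

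**What to change.** 1. In the section on the effectiveness of the programme, replace the attribution to lifestyle with: uncontrolled change from baseline in the coaching-plus-placebo arm, not attributable to coaching alone.
2. State that the t0 sample, separate from the qualifying value, is the baseline for this analysis.
3. Present the direct and modelled economic analyses of the coaching programme as exploratory scenarios, and include one in which coaching has no effect.
4. For the zinc cost-consequence model, say explicitly that its effect input is the whole-arm randomised contrast used in the Direct analyses section.

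These are changes of wording and model input. The Fig. 1 legend already lists HbA1c at t0, so no additional sample should be needed if that one is distinct from the screening test. The cost is a weaker claim about the coaching service.

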#### Cost-effectiveness of zinc and Get Healthy T2DM Prevention Program

##### Direct analyses

The cost-effectiveness of zinc supplementation will be assessed in a trial-based analysis. The analysis will adopt a modified societal perspective to account for health care system costs as well as patient costs which would be incurred if the zinc supplement were an out-of-pocket expense. The incremental cost-effectiveness ratio (ICER) will be calculated as the difference in average cost between the zinc supplementation group and the placebo group, divided by the difference in average FPG level. Uncertainty intervals for the incremental costs and ICER will be calculated using a non-parametric bootstrap procedure to reflect sampling uncertainty. Sensitivity analysis will examine imputation uncertainty, comparing the reference case results with the analysis of participants with complete data. Additional sensitivity analysis will involve variation in the market price of zinc capsules.

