**Fig. 1 Fig1:**
[figure not shown]
Participant timeline. Standard Protocol Items: Recommendations for Interventional Trials (SPIRIT) figure [20] (Additional file 1) for the study schedule of enrolment, interventions and assessments. Baseline assessments will occur at -t_1–0_ prior to allocation. Follow-up will occur at time points between t_1_ and t_5_ (1, 3, 6, 9 and 12 months after allocation). Adverse event monitoring will occur after allocation at t_2_, t_3,_ t_4_ and t_5_ (3, 6, 9 and 12 months); HbA1c, LDL, HDL, total cholesterol, triglycerides, fasting blood glucose and insulin will be collected at –t_1–0_, t_0_ (baseline), t_1_ (1 month) t_3_ (6 months) and t_5_ (12 months). Close-out assessments will occur at t_5_ (12 months)

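### The ICER's effect term names no use of baseline fasting glucose, so it is less precise than the trial's own data allow and carries any chance baseline imbalance

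*Protocol article*

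**What the plan says.** Under Direct analyses, the protocol article gives a formula for the ICER of zinc. It is "calculated as the difference in average cost between the zinc supplementation group and the placebo group", "divided by the difference in average FPG level". That section does not mention baseline FPG, change from baseline or covariate adjustment. It does not give the order of subtraction for FPG.

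For uncertainty it states: "Uncertainty intervals for the incremental costs and ICER will be calculated using a non-parametric bootstrap procedure to reflect sampling uncertainty". Two sensitivity analyses are named. One compares the reference case with participants who have complete data. The other is described thus: "Additional sensitivity analysis will involve variation in the market price of zinc capsules". Neither concerns baseline glucose.

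Elsewhere the article does use baseline values. The Primary analysis section says that "the model will be adjusted for baseline HbA1c or IS, age, sex, physical activity and diet". The caption of Fig. 1 says "HbA1c, LDL, HDL, total cholesterol, triglycerides, fasting blood glucose and insulin will be collected at" baseline and at 1, 6 and 12 months. According to Trial design, randomisation is stratified by GP practice and sex, and so not by glucose.

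**The concern.** A participant's fasting glucose at follow-up depends strongly on the value at entry. A comparison of average levels that leaves out the entry value has two costs. It keeps variance that a covariate already in the database would remove. It also lets any chance baseline difference between the arms pass, in part, into what is reported as the effect of zinc. Stratification by practice and sex does little to prevent such a difference.

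Both costs matter more than usual here because the quantity is the denominator of a ratio, where noise in a small number is magnified. The economic effect estimate would also be of a different type from the trial's baseline-adjusted clinical estimates, and neither planned sensitivity analysis would show the gap. Cost-effectiveness is a listed secondary objective.

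**Working it through.** **The plan's own figures.** The article gives no cost, FPG or ICER figure to reproduce. The only figure used below is 164 analysed per group (Sample size). It reproduces: a difference of 0.3, SD 0.7, two-sided alpha 0.01 and power 0.9 give 163 per group by the normal formula and 163.7, so 164, by the t-test. Then 328/0.8 = 410. These figures concern insulin sensitivity; only the group size carries over.

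**Assumptions.** The baseline-to-follow-up correlation r of FPG is taken as 0.5 to 0.7. The SD is taken as equal at both times, the slope as common to both arms, and FPG as the same measurement as the fasting blood glucose in Fig. 1.

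**Precision.** In SD units, with n = 164 per arm:

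- Unadjusted SE of the FPG difference = √(2/n) = √(2/164) = 0.110.
- Baseline-adjusted SE = √(2/n) × √(1 − r²).
- Proportion of variance removed = r².

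| r | Adjusted SE | Variance removed |
|---|---|---|
| 0.5 | 0.096 | 25% |
| 0.6 | 0.088 | 36% |
| 0.7 | 0.079 | 49% |

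At r = 0.6 the gain equals that of raising the group size from 164 to 164/0.64 = 256.

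**Carry-over of a chance imbalance.** The SE of the baseline difference is also 0.110 SD. An unadjusted follow-up difference takes up r times the realised baseline difference:

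- For an imbalance of one SE: 0.055 SD at r = 0.5 and 0.077 SD at r = 0.7.
- For an imbalance of 1.96 SE: 0.11 SD at r = 0.5 and 0.15 SD at r = 0.7.

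In glucose units, take an assumed SD of 0.6 mmol/L. The SE of the baseline difference is 0.6 × 0.1104 = 0.066 mmol/L. At r = 0.6, a one-SE imbalance carries over 0.6 × 0.066 = 0.040 mmol/L. That is 27% of an assumed effect of 0.15 mmol/L, 13% of 0.3 and 40% of 0.1. The carry-over scales in proportion to the SD.

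**Average and conditional behaviour.** A simulation used 164 per arm, r = 0.7 and an assumed true effect of −0.40 SD.

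- Over all randomisations, both estimates averaged −0.40. The SE was 0.110 unadjusted and 0.079 adjusted.
- Where the baseline difference was about +0.2 SD, the unadjusted mean was −0.26 (−0.40 + 0.7 × 0.2) and the adjusted mean −0.40. With the same cost difference, the ratio is then larger in size by 0.40/0.26 = 1.54. An imbalance of this size is 0.2/0.110 = 1.8 SE, so it is on the large side. An imbalance of the opposite sign would flatter zinc.

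**Sign.** For an assumed extra cost of 100, if both differences are zinc minus placebo:

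- FPG difference −0.3 (benefit): 100/(−0.3) = −333.
- FPG difference +0.3 (harm): 100/0.3 = +333.

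With a saving of 100 and benefit, the ratio is (−100)/(−0.3) = +333. The negative sign for benefit therefore needs both that order of subtraction and a positive incremental cost. The size of the ratio is the same under either order.

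**The case against.** The strongest reply is that the sentence is a summary and does not say that the FPG difference is unadjusted. A difference in average level can come from a model. The Secondary analyses section describes a mixed model that uses baseline data for secondary outcomes, and fasting blood glucose is listed among these. A condensed article may also leave covariates to a fuller plan. This stands in part: that the difference is crude is an inference from the wording. But the article states a formula for the ratio, and a fuller plan that followed it would have no baseline term.

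The second reply is that chance imbalance is ordinary sampling variation, which the bootstrap already reflects. This is correct. Randomisation makes the unadjusted difference unbiased, and its interval includes the imbalance. What remains is lost precision, and error conditional on the imbalance that actually occurs.

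The third is that the size rests on assumed values. That is also true; the article gives no FPG SD, correlation, effect or cost.

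Two stronger readings are tempting, and the article supports neither:

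- A reader might infer that the ratio will have the wrong sign. The article gives no order of subtraction for FPG, the reversal also needs zinc to cost more, and the size of the ratio does not change. This is a reporting convention.
- A reader might infer that an error passes into the 5-year and lifetime models. The Modelled analyses section says trial results will be extrapolated, but not that this ratio or its sign is an input.

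**Conclusion.** The point holds as a matter of efficiency and of conditional error. The stated effect term makes no use of a baseline measurement that the trial collects and that its primary model type would use. Adjustment would reduce the variance of the FPG difference by r², which is 25% to 49% for r of 0.5 to 0.7. It would also remove the part of any chance baseline imbalance that would otherwise pass into the denominator. These figures rest on the assumed correlation, on equal SDs and on 164 analysed per arm. The planned estimate is not biased over randomisations and its bootstrap interval is not invalid. The sign convention is a minor labelling matter. This is a worthwhile improvement to a secondary economic analysis.

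**What to change.** In Direct analyses, define the ICER denominator as the baseline-adjusted reduction in FPG, placebo minus zinc, at a named follow-up time. Estimate it by regressing follow-up FPG on arm, baseline FPG and covariates measured at baseline only, such as age and sex. Physical activity and diet should enter only as baseline values: the Primary analysis section does not say when they are measured, and adjusting for values recorded after randomisation could distort the effect. Refit the regression in every bootstrap replicate and compute the cost difference in the same replicate, so that the correlation between cost and effect is kept.

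Stated this way, a positive ratio with a positive incremental cost reads as extra cost per mmol/L lowered. Writing it down before unblinding also removes a later choice between an adjusted and an unadjusted ratio. The cost is a sentence or two in the plan and one regression per replicate, with no new data.

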### Sample size

The sample size is based on an estimated mean difference in IS of 0.3 (with SD of 0.7, equal to Cohen’s *d* of 0.4) between the intervention and control groups. We will need 164 participants per group to reject the null hypothesis that the intervention and control group means are equal with probability (power) 0.9 and type I error probability (α) of 0.01. Allowing up to 20% loss to follow-up over 1 year, we will need to recruit a total of 410 participants.

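### The planned bootstrap interval on the ICER will not rank value for money if the fasting glucose difference in its denominator spans zero; net benefit from the same replicates avoids this

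*Protocol article*

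**What the plan says.** The Direct analyses section of the protocol article defines the ICER through its numerator, "calculated as the difference in average cost between the zinc supplementation group and the placebo group", and its denominator, "divided by the difference in average FPG level". It then fixes how uncertainty is to be expressed: "Uncertainty intervals for the incremental costs and ICER will be calculated using a non-parametric bootstrap procedure to reflect sampling uncertainty". The interval is therefore promised for the ratio itself as well as for the cost difference. The section does not name the type of bootstrap interval. It does not say whether the glucose difference is adjusted for baseline, or what is reported if that difference could have either sign.

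No expected difference or SD for fasting glucose appears anywhere. The only planning effect is for insulin sensitivity, in Sample size: "The sample size is based on an estimated mean difference in IS of 0.3", with an SD of 0.7. The legend of Fig. 1 lists fasting blood glucose among the baseline measurements. I take FPG in the economic section to be that same measurement.

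**The concern.** An ICER is easy to interpret while the effect difference is clearly on one side of zero. Once bootstrap differences fall on both sides, the ratio runs off towards plus infinity on one side of zero and minus infinity on the other. Sorting the replicates by ICER then no longer sorts them by value for money. A negative ICER can mean that zinc costs less and works better, or that it costs more and works worse. A positive one can mean a benefit bought at a price, or a saving with a worse effect.

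The difficulty remains if zinc always adds cost. The replicates in which it costs more and works worse then have negative ICERs. They sit at the low end of the range, where a reader expects the best value.

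Cost-effectiveness is a stated secondary objective, and Modelled analyses extrapolates from the trial-based result. A finite interval that looks ordinary but is not ordered by value could mislead there.

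**Working it through.** **Reproducing the plan's own figure.** The inputs from Sample size are a difference of 0.3, an SD of 0.7, power "with probability (power) 0.9" and "type I error probability (α) of 0.01". Two-sided testing is my assumption, because sidedness is not stated.

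- Normal formula: n = 2 × (2.576 + 1.282)² × (0.7/0.3)² = 162.02, so 163 per group.
- The t-based calculation gives 163.7, so 164, which agrees with "We will need 164 participants per group".
- Allowing for 20% loss: 328 / 0.8 = 410, as stated.

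The arm size of 164 is therefore sound to carry forward.

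**Precision of the denominator.** In SD units, the SE of an unadjusted mean difference is sqrt(2/164) = 0.110.

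**How often the denominator spans zero.** Let d be the true standardised fasting glucose benefit (assumed, since the documents give none) and z = d/0.110. More than 2.5% of bootstrap differences lie on each side of zero when the estimate is within 1.96 SE of zero. The probability of this is Φ(1.96 − z) − Φ(−1.96 − z). The average share of replicates on the wrong side, taken over trials, is Φ(−z/√2).

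| d (assumed) | z | Average wrong-side share | Trials with more than 2.5% on each side |
|---|---|---|---|
| 0 | 0 | 50% | 95% |
| 0.1 | 0.91 | 26% | 85% |
| 0.2 | 1.81 | 10% | 56% |
| 0.3 | 2.72 | 3% | 22% |
| 0.4 | 3.62 | 0.5% | 5% |
| 0.43 (insulin sensitivity effect, 0.3/0.7) | 3.88 | 0.3% | 3% |

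A simulation with real resampling (200 trials, 1,000 resamples each) gave 92.5%, 82%, 51.5% and 2.5% for the last column at d = 0, 0.1, 0.2 and 0.43. This agrees within simulation error.

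**What the interval looks like.** This illustration rests on assumed values: an observed cost difference of 100 with SD 500, an observed glucose benefit of 0.1 SD, independent errors and 164 per arm.

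- SE of the cost difference: 500 × 0.110 = 55.
- Point ICER: 100/0.1 = 1,000 per SD of glucose.
- Percentile interval under the normal approximation: about −9,200 to +10,200.
- About 20% of replicates are negative: 18% where zinc costs more and works worse, and 3% where it costs less and works better (figures rounded).

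The lower end looks like a saving, but most of the negative replicates are the worst outcome.

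**What baseline adjustment buys.** If baseline and follow-up glucose correlate at ρ, adjustment multiplies the SE by sqrt(1 − ρ²): 0.87 at ρ = 0.5 and 0.71 at ρ = 0.7 (assumed values). At d = 0.2, z rises to 2.09 or 2.54, and the share of trials affected falls from 56% to 45% or 28%. At d = 0 it stays at 95%. Adjustment reduces the problem but does not remove it.

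**The case against.** The strongest reply is that the failure is conditional. If the planning effect for insulin sensitivity carried over to fasting glucose, only about 3% of trials would be affected, and the Rationale cites meta-analyses that found lower fasting glucose with zinc. That stands as a limit on the claim. A reader might infer that the interval is bound to be unreadable; the documents do not support this, because they give no glucose effect. They do not support the reassurance either. Nothing ties the insulin sensitivity effect to glucose, and the Discussion says the earlier trial populations were more likely to be zinc deficient than Australians.

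A second reply is that bootstrapping is standard, and that the plane, acceptability curve and net benefit are reporting details a condensed article may leave to a fuller plan. Their absence is indeed no finding. The point concerns what the article does state, an interval on the ratio. The resampling itself is sound.

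A third reply is that readers will also see an interval for incremental cost and a between-group analysis of fasting glucose. This helps, but separate margins do not show the joint uncertainty, and the ICER interval would still be printed.

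Three further inferences go beyond the text:

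- **The glucose difference is unadjusted.** The section does not say so. An unadjusted difference would also be unbiased in a randomised trial, so adjustment is a matter of precision.
- **The interval is a percentile interval.** The type is not named.
- **No bounded interval exists.** That is true of a valid confidence set for the ratio. An interval formed by ordering replicates is always finite, which is why it can mislead.

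Modelled analyses says it will "transform the intermediate, primary trial outcome into a final, patient-relevant outcome" without naming the variable. The article's differing statements of its primary outcomes are a separate issue and carry no weight here.

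**Conclusion.** The point holds conditionally and is of low priority. The article commits to an interval on a ratio whose denominator may not be clearly separated from zero at this sample size. If the standardised glucose effect is about 0.2 or less, an interval from ordered ICER replicates would fail to rank value for money in more than half of trials (56% at 0.2, 85% at 0.1, 95% at 0). At 0.4 the figure is about 5%.

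These figures rest on an assumed range for the glucose effect, 164 evaluable participants per arm, approximate normality of the mean difference and an unadjusted comparison. The interval widths in the illustration also depend on invented costs and show only the mechanism. The efficacy conclusions are not touched.

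**What to change.** Keep the ICER as a point estimate. In place of the interval on the ratio, report from the same bootstrap replicates:

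- the cost-effectiveness plane;
- the incremental net benefit with its bootstrap interval, or the acceptability curve, over a stated range of willingness-to-pay values per unit of fasting glucose.

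Net benefit is linear in the cost and effect differences, so its interval remains valid whatever the sign or size of the glucose effect. The planned interval for incremental costs can stay. State that the glucose difference is estimated with adjustment for baseline fasting glucose, re-estimated within each replicate.

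The cost is a few lines of analysis code and no new data. The real downside is that a willingness-to-pay range per unit of glucose has to be chosen and justified.
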